### Study design

2.1

This study is an outcome assessor and data analyst-blinded, randomized, controlled superiority trial and will be conducted at the Second Affiliated Hospital of Qiqihar Medical University, from October 2021 to December 2023. CP patients who meet the inclusion criteria will be allocated in a 1:1 ratio into the treatment group (hydrotherapy plus tDCS, n = 75, expected), or the control group (treatment as usual, n = 75, expected). All participants will receive 30 sessions of treatment over 10 weeks. The study design is presented in Figure 1.

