### Outcome measures

2.6

We will evaluate the CP children using questionnaires at the beginning of the treatment, within 1 week after 10 weeks of therapy, 4 weeks, and 12 weeks after the last intervention. Descriptive measures and characteristics, such as age, gender, body weight, type of CP and the outcomes were recorded for all study participants. All patient related data will be safely collected and stored. Only researchers related to the study will be allowed to access to the trial dataset. The primary outcomes of this study are Gross Motor Function Assessment and Pediatric Balance Scale (PBS) between the treatment group and the control group. The secondary outcomes are the difference in Pediatric Evaluation Disability Inventory (PEDI), adverse effects between the control and treatment groups.

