#### Control group: usual care

2.7.1

Both groups of participants will continue to receive “usual care” during the 10-week intervention. Usual care refers to any therapeutic treatment or service that the child would normally receive outside of the intervention study. The researcher will evaluate children's condition, we expected that most participants in this study will not access additional therapy as possible.

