### Statistical analysis

2.8

An experienced statistician will conduct the data analysis. When necessary, intention to treat analysis will be used with the data from the previous evaluation repeated to substitute missing data. We will use the Kolmogorov-Smirnov test to demonstrate normal data distribution. Thus, Parametric data will be presented as mean (standard deviation) as well as nonparametric data will be presented as median (inter-quartile interval). The effect size will be calculated by the difference between means of the pre-intervention and post-intervention evaluations and will be presented with the respective 95% confidence interval. The independent *t* test and chi-square tests will be applied to assess and compare the baseline patient characteristics between the treatment and the control groups. Either 2-way ANOVA or the Kruskal-Wallis test will be used for the statistical analysis of the effects of control group or treatment group for parametric and nonparametric variables, respectively. The Bonferroni correction for multiple comparisons will be employed as the post hoc test. Statistical significance will be considered at a *P* value of <.05. The data will be organized and tabulated using the Statistical Package for the Social Sciences (SPSS) version 19.0 (IBM, Armonk, NY, USA).

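### The effect size and its 95% CI are defined as a pre-to-post difference with no contrast between arms, so the reported effect would include change that occurs under usual care

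*Protocol article*

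**What the plan says.** Section 2.8 (Statistical analysis) gives one definition of the effect: "The effect size will be calculated by the difference between means of the pre-intervention and post-intervention evaluations". The same sentence adds that it "will be presented with the respective 95% confidence interval". No group is mentioned. The sentence also does not say which of the three post-treatment assessments it means.

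Elsewhere the article sets a comparison between randomised groups. Section 2.1 (Study design) describes an "outcome assessor and data analyst-blinded, randomized, controlled superiority trial". Section 2.6 (Outcome measures) states: "The primary outcomes of this study are Gross Motor Function Assessment and Pediatric Balance Scale (PBS) between the treatment group and the control group".

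Section 2.8 also plans a test: "Either 2-way ANOVA or the Kruskal-Wallis test will be used for the statistical analysis of the effects of control group or treatment group", with Bonferroni correction for the post hoc comparisons. The ANOVA factors are not named, and no estimate or interval is tied to this test.

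Section 2.7.1 states: "Both groups of participants will continue to receive “usual care” during the 10-week intervention".

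**The concern.** A superiority trial has to report how much better one arm does than the other, and how precisely that is known. A pre-to-post difference in means does not answer that question. In the treatment arm it is the sum of the treatment effect and everything else that moves the score over the same period. Here that includes continuing usual care, development in children aged 4 to 14, and repeated administration of the scales. The control arm is there to remove this background change, and the defined effect size does not use it.

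The estimate would be the published size of benefit for both primary outcomes, GMFM-88 and PBS. A valid group P value printed beside a within-arm effect and interval would leave readers, and later meta-analyses, with the wrong magnitude and an interval that looks too narrow.

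**Working it through.** The article states no expected effect, SD, pre-post correlation or background change, so there is no figure of its own to reproduce. The check is algebraic, followed by an illustration on assumed values.

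**What each quantity estimates.** Let b be the background change common to both arms and δ the treatment effect.

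- Pre-to-post change, treatment arm: b + δ
- Pre-to-post change, control arm: b
- Difference in change between arms: (b + δ) − b = δ

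Only a between-arm contrast (difference in change, or a baseline-adjusted difference) removes b.

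**Inputs for the illustration.**

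- n = 75 per arm: section 2.1.
- 95% interval: section 2.8, taken as two-sided.
- δ = 0, b = 0.1 to 0.3 SD, pre-post correlation r = 0.5 to 0.9, equal SD at both times and in both arms: assumptions, not in the documents.

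**Formulas** (SD units, normal approximation).

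- SD of the change: √(2(1 − r))
- SE of the within-arm change: √(2(1 − r)/75)
- SE of the between-arm difference in change: √(2(1 − r)) × √(2/75)
- Chance that the within-arm interval excludes zero: Φ(b/SE − 1.96) + Φ(−b/SE − 1.96)

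**Worked case, r = 0.7 and b = 0.2.** SE = √(0.6/75) = 0.0894. Then b/SE = 2.24, and Φ(2.24 − 1.96) = Φ(0.28) ≈ 0.61; the second term is negligible.

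**Chance that the pre-post interval excludes zero when the treatment does nothing.**

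| r | b = 0.1 | b = 0.2 | b = 0.3 |
|---|---|---|---|
| 0.5 | 0.14 | 0.41 | 0.74 |
| 0.7 | 0.20 | 0.61 | 0.92 |
| 0.9 | 0.49 | 0.97 | about 1.00 |

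For the between-arm contrast the chance is 0.05 throughout. With b = 0 the pre-post interval also gives 0.05, so the excess comes entirely from background change.

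**Half-width of the 95% interval (SD units).**

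| r | Within arm | Between-arm difference in change |
|---|---|---|
| 0.5 | 0.226 | 0.320 |
| 0.7 | 0.175 | 0.248 |
| 0.9 | 0.101 | 0.143 |

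The ratio is √2 ≈ 1.41 in each row, so the interval as defined understates the uncertainty of the treatment comparison by that factor.

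**The case against.** The strongest reply is that the arms are compared. Section 2.8 plans an ANOVA or Kruskal-Wallis test of the group effects, and nothing in the article says superiority will be judged from pre-post intervals. That stands. A reader might infer that the trial has no between-group test, or that benefit will be claimed because one arm changed and the other did not; the document supports neither. A reader might also infer that the between-arm effect cannot be recovered at all. If the change is reported for each arm, its point value follows by subtraction. What is missing from the stated definition is the contrast itself and its interval, and the planned test does not supply them.

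Second, the sentence never says that the difference is taken within a group, and may have been meant as a between-arm difference in change. The between-group wording of the primary outcomes favours that intention. But the sentence names only time points, and an analyst following it literally would compute a pre-post difference. If the between-arm reading was intended, the correction is a clarification.

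Third, an unseen analysis plan might handle this. That would answer an omission, but here the protocol states a definition, and a plan that defined a between-arm effect would depart from it.

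Fourth, the background change is unknown. That is true, and the percentages are illustrative only. Regression to the mean should not be leaned on either: section 2.2 sets no GMFM or PBS threshold for entry, so children are not selected for extreme scores on those scales.

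**Conclusion.** The concern holds, limited to the defined effect estimate and its confidence interval. As worded, section 2.8 reports a pre-to-post difference where a randomised superiority comparison needs a between-arm one. The planned group test is a separate matter and is not shown to be invalid by this point.

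The bias in the treatment-arm figure equals the background change, whose size the documents do not give. With an assumed background change of 0.2 SD, no treatment effect and 75 children per arm, the pre-post interval excludes zero about 41% of the time at a correlation of 0.5 and 97% at 0.9, against 5% for the between-arm contrast. At 0.1 SD and a correlation of 0.5 the figure falls to 14%; with no background change the excess disappears. It would be tempting to quote a single multiple by which the effect is inflated, but any such multiple depends wholly on the gains one assumes. The structural point needs none of these values: the defined quantity is b + δ in the treatment arm, and the trial's question is δ.

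**What to change.** Restate the sentence in section 2.8 along these lines: the effect size for GMFM-88 and for PBS is the difference between the treatment and control groups, either adjusted for the baseline score or taken as the difference in pre-to-post change, with its 95% confidence interval, at a post-treatment visit named in advance; changes within each group are descriptive only.

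The sponsor has to name that visit, because sections 2.5 and 2.6 schedule three post-treatment assessments (1, 4 and 12 weeks after treatment ends) and designate none as primary. The 1-week visit is one possible choice. The choice between baseline adjustment and difference in change should also be recorded before the data are analysed. If the nonparametric branch is kept, the text should say which between-group estimate accompanies it.

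No new data, visits or children are needed. The costs are a wider interval than the one now described (about 1.4 times for the difference in change) and the commitment to one visit. The wider interval is the correct statement of uncertainty for the comparison between arms.

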#### Primary outcomes measures

2.6.1

Gross Motor Function Measure 88 (GMFM-88): The GMFM-88 will be used to detect gross motor function change in this study.^[36–38]^ The GMFM-88 is made up of 5 dimensions that can be analyzed separately or combined to produce a total GMFM-88 score. The 5 dimensions are as follows: lying and rolling, sitting, crawling and kneeling, standing, and walking, running, and jumping. All items are scored on a 4-point scale, the higher the score, the better the function.^[36–38]^ The treating therapist, in collaboration with parents and children, will choose Gross motor goal dimensions while considering the age of children and gross motor function classification system level. All evaluation process will be recorded and later scored by a senior physiotherapist who is blind to group allocation. The results will be reported as percentage scores.

PBS: The same blinded researcher will administer the PBS before and after the intervention.^[39–41]^ To assess balance, the PBS will be used, which is composed of 14 items. The items assess the functional activities which children could perform to function within the home, school, or community safely and independently. This scale has also been tested for children with CP and has good test–retest and interrater reliability when used assess participation of school-age children with mild to moderate movement disorder.^[39–41]^

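### Baseline characteristics are used only for significance tests between randomised arms, and the outcome analysis names no adjustment for the recorded age and type of CP (minor)

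*Protocol article*

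**What the plan says.** **Baseline data.** Section 2.6 (Outcome measures) states: "Descriptive measures and characteristics, such as age, gender, body weight, type of CP and the outcomes were recorded for all study participants". Four characteristics are named besides the outcomes, and the list is open-ended. In section 2.8 (Statistical analysis) the only stated use of such data is a comparison of the arms: the independent t test and "chi-square tests will be applied to assess and compare the baseline patient characteristics between the treatment and the control groups". No consequence is attached to the results. The threshold given in that section is "Statistical significance will be considered at a *P* value of <.05".

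**Allocation.** Section 2.1 says that patients "will be allocated in a 1:1 ratio into the treatment group" or the control group. Section 2.4 places the first assessment before allocation and describes numbered, sealed, opaque envelopes. No stratification factor is named.

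**Outcome analysis.** Section 2.8: "Either 2-way ANOVA or the Kruskal-Wallis test will be used for the statistical analysis of the effects of control group or treatment group", according to whether the variable is parametric. The second ANOVA factor is not named. On the effect size: "The effect size will be calculated by the difference between means of the pre-intervention and post-intervention evaluations". No covariate appears.

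**Motor severity.** Section 2.6.1 mentions the gross motor classification level once: the treating therapist, with parents and children, "will choose Gross motor goal dimensions while considering the age of children and gross motor function classification system level". The level is not among the characteristics that section 2.6 names as recorded.

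**The concern.** A significance test asks whether a difference is larger than chance would produce. Between properly randomised arms chance is the only source of a baseline difference, so the answer is known beforehand. A P value below .05 is then a false alarm. One above .05 says little about comparability, because at 75 per arm a difference large enough to matter can pass.

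The better use of these variables is in the outcome model. Section 2.2 admits children of 4 to 14 years with any type of CP and sets no limit on motor severity. Change in gross motor function and balance may well depend on age and type. A model that includes such factors removes their chance imbalance from the treatment estimate and narrows the confidence interval to the extent that they predict the outcome. The article names no such adjustment. If an imbalance appears, nothing fixed in advance says what will be done about it.

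**Working it through.** **Inputs from the article:** 150 children, 75 per arm (2.1, 2.3); threshold .05 (2.8), taken as two-sided because sidedness is not stated; four named characteristics plus the outcomes (2.6); ages 4 to 14 (2.2); spastic share 58.86% (Discussion).

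**The plan's own figure.** The 150 cannot be reproduced, since no effect size, SD, power or dropout is given. Read backwards with the normal approximation, 75 per arm matches a standardised difference of (1.96 + 0.84) × √(2/75) = 0.457 at 80% power, or 0.529 at 90%. The point does not depend on this figure.

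**1. False alarms when every null hypothesis is true.** For k independent tests, P(at least one P<.05) = 1 − 0.95^k.
- k = 4 (age, gender, body weight, CP type): 1 − 0.95⁴ = 18.5%; expected number 4 × 0.05 = 0.20.
- k = 7 (adding GMFM-88, PBS, PEDI): 1 − 0.95⁷ = 30.2%; expected number 7 × 0.05 = 0.35.

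The seven are unlikely to be independent. With an assumed correlation within the three functional scales and between age and weight, simulation gives about 28% at a correlation of 0.5 and 23% at 0.9. So 30% is an upper figure.

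**2. What the tests let through.**
- Age, assumed uniform on 4 to 14: SD = 10/√12 = 2.89; SE of the difference = 2.89 × √(2/75) = 0.471; 1.96 × 0.471 = 0.92. Mean ages up to about 0.9 years apart are not flagged.
- CP type (spastic or not) at 58.86%: SE = √(2 × 0.5886 × 0.4114/75) = 0.0804; 1.96 × 0.0804 = 0.158. A difference must exceed about 15.8 percentage points to be flagged. Under simple randomisation one of 10 points or more has probability 2 × [1 − Φ(0.10/0.0804)] = 21%.

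**3. What adjustment could gain.** If covariates explain a fraction R² of the outcome variance, the SD becomes SD × √(1 − R²). The article gives neither R² nor a target difference, so these are illustrations at an assumed true difference of 0.4 SD, two-sided .05:

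| Assumed R² | Power, 75 per arm | n per arm for 80% power |
|---|---|---|
| 0 | 68.8% | 99 |
| 0.10 | 73.3% | 89 |
| 0.25 | 80.7% | 74 |

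At an assumed 0.3 SD, power goes from 45.1% (R² = 0) to 49.1% (0.10) and 56.4% (0.25). At 0.5 SD it goes from 86.5% to 89.8% and 94.2%.

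**4. What adjustment could cost.** With N = 150 and k covariates of no predictive value, the variance of the treatment estimate rises on average by the factor (N − 3)/(N − 3 − k). For k = 2 this is 147/145 = 1.014, an increase of about 1%. For k = 3 it is 147/144 = 1.021.

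**The case against.** The strongest reply has four parts.

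- **Covariate lists often sit in an analysis plan that is not shown, and an article condenses.** This stands in part. A reader might infer that age and CP type never enter the outcome analysis; the article does not support that. The second ANOVA factor is unnamed, pre-intervention scores may enter through the pre/post comparison, and an unseen plan could add covariates. What can be said is that the article names no adjustment. It is still fair to raise, because section 2.8 does state its method, and one branch of it, Kruskal-Wallis, cannot take covariates.

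- **No validity error follows.** This stands. A reader might infer a biased treatment effect. An unadjusted randomised comparison is unbiased, and its standard error already allows for chance imbalance. The baseline tests alter no estimate, and section 2.8 ties no decision to them. That someone might later adjust for whatever reached P<.05 is a possibility, not something the article plans; section 2.4 also keeps the statistician unaware of the grouping.

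- **A baseline difference could reveal failed concealment.** This stands as a qualification. The null hypothesis is true by design only if allocation was not subverted. The article does not offer the tests for that purpose.

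- **Severity level may not be collected as data.** This stands. "while considering the age of children and gross motor function classification system level" shows that therapists take the level into account, which may tempt a reader to count it as a recorded prognostic factor. Section 2.6 does not list it.

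**Conclusion.** The point holds as a minor weakness of method. The planned baseline tests are uninformative under concealed randomisation, with about an 18.5% chance of at least one false alarm over the four named characteristics if independent. The figure of about 30% needs seven independent tests and should not be the headline. The stated outcome analysis names no adjustment for age and type of CP, both of which are recorded.

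The consequence is limited to lost precision and the absence of a pre-specified way to handle chance imbalance. The precision loss cannot be sized from the article. A reader might want a definite saving in children or a definite variance reduction, but any such number rests on assumed growth patterns or an assumed R², and the plausible range includes no gain at all. The power figures above are illustrations only. The age figure rests on an assumed uniform distribution, and the CP-type figures on simple randomisation with the national spastic share quoted in the Discussion.

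**What to change.** 1. In section 2.8, remove the baseline t and chi-square tests. Present baseline data by arm as descriptive statistics without P values.
2. State that the primary GMFM-88 and PBS analyses use a linear model (ANCOVA-type, or mixed for the repeated evaluations) with age and type of CP as covariates, included whatever imbalance is observed.
3. If the gross motor classification level is recorded at baseline, list it in section 2.6 and include it in the same model. If it is not, consider adding the field, since therapists already take it into account.

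**Cost:** about two sentences and at most one baseline field. Statistically it takes a few degrees of freedom: about 1% of variance if age and one CP-type term predict nothing, and about 2% with a third such term. Dropping the tests changes no treatment estimate; fixing the covariates in advance is the part that can improve the analysis.

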### Evaluation and follow-up

2.5

Two experienced physical therapists who blind to which group each child belongs will evaluate the both group in the evaluation procedures. Four evaluations will be conducted:

First evaluation: 1 week before intervention;Second evaluation: 1 week after the last intervention;Third evaluation: 4 weeks after the last intervention;Fourth assessment: 12 weeks after the last intervention.These evaluations will be conducted on 2 nonconsecutive days.

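### Section 2.8 names 2-way ANOVA or Kruskal-Wallis for four correlated scores per child without a within-child factor, a deciding contrast or baseline adjustment, and lets a normality test choose between them

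*Protocol article*

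**What the plan says.** Section 2.5 (Evaluation and follow-up) states "Four evaluations will be conducted". The first is before treatment ("First evaluation: 1 week before intervention"), and the others come 1, 4 and 12 weeks after the last session. Section 2.6 gives two primary outcomes and no primary visit: "The primary outcomes of this study are Gross Motor Function Assessment and Pediatric Balance Scale (PBS) between the treatment group and the control group".

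Section 2.8 (Statistical analysis) handles these data as follows:

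- Normality check: "We will use the Kolmogorov-Smirnov test to demonstrate normal data distribution".
- Test of the arms: "Either 2-way ANOVA or the Kruskal-Wallis test will be used for the statistical analysis of the effects of control group or treatment group", the first for parametric and the second for nonparametric variables.
- Multiplicity: "The Bonferroni correction for multiple comparisons will be employed as the post hoc test".
- Threshold: "Statistical significance will be considered at a *P* value of <.05".
- Use of the pre-treatment score: "The effect size will be calculated by the difference between means of the pre-intervention and post-intervention evaluations", with a 95% CI. This is neither described as a contrast between arms nor linked to either test.

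The two factors of the ANOVA are not named, and neither a repeated-measures nor a mixed model is mentioned. The Introduction states the hypothesis as greater and more durable improvement in motor function, which is a question about change over time.

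**The concern.** Four scores from one child are correlated. An ordinary 2-way ANOVA takes the 150 × 4 = 600 scores as independent, so it misjudges the variance of both the group effect and the interaction, in opposite directions. A mixed ANOVA repairs this, but it offers two tests of the arms that answer different questions. Its group main effect averages the pre-treatment visit, at which no effect can exist, into the treatment effect. The Kruskal-Wallis alternative has one factor and no place for visit, so it cannot test the same hypothesis as group-by-time. No stated test adjusts for the pre-treatment score, although every child is due to have one.

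The P value behind the main claim therefore depends on choices that section 2.8 leaves open. If GMFM-88 passes the normality check and PBS fails it, or the reverse, the two primary outcomes would be tested under different hypotheses.

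**Working it through.** **Inputs from the protocol.** 75 children per arm (section 2.1), four scores per child (section 2.5), alpha 0.05 (section 2.8; two-sided assumed).

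**The plan's own figure.** Section 2.3 gives N = 150 but no effect size, SD, power or dropout, so it cannot be reproduced. For scale, 75 per arm detects 0.457 SD with 80% power on one post-treatment score without baseline.

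**Assumptions, not in the protocol.** Normal data, equal correlation rho between any two scores of a child, no missing scores, and an effect of d = 0.3 SD at all three post-treatment visits. Write k = √(75/2) = 6.124.

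**Formulas, with rho = 0.8 put in**

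1. *Ordinary ANOVA, group effect.* The true variance is (1 + 3rho) times the assumed one. Type I error = 2[1 − Φ(1.96/√(1 + 3rho))] = 2[1 − Φ(1.96/1.844)] = 29%.
2. *Ordinary ANOVA, group-by-time.* The statistic is shrunk by (1 − rho), so 7.815 becomes 7.815/0.2 = 39.1 on 3 df. Type I error is below 0.1%. Power uses noncentrality 37.5 × 0.75d²/(1 − rho) = 37.5 × 0.0675/0.2 = 12.66, giving about 1%.
3. *Mixed ANOVA, group main effect.* The effect is 0.75d = 0.225 and the variance (1 + 3rho)/4 = 0.85. Power = Φ(0.225 × 6.124/0.922 − 1.96) = Φ(−0.466) = 32%.
4. *Mixed ANOVA, group-by-time.* F with 3 and 444 df and the same noncentrality of 12.66: power 86%.
5. *One post-treatment score.* The t test has 45% power. The rank test gives Φ(0.3 × 6.124 × √(3/π) − 1.96) = Φ(−0.165) = 43%. About 44% is used below; it does not depend on rho.
6. *ANCOVA on one post-treatment score.* Φ(0.3 × 6.124/√(1 − rho²) − 1.96) = Φ(3.062 − 1.96) = 86%.

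| rho | Ordinary ANOVA, group: type I error | Ordinary ANOVA, group-by-time: power | Mixed ANOVA, group: power | Mixed ANOVA, group-by-time: power | Rank test, post score: power | ANCOVA: power |
|---|---|---|---|---|---|---|
| 0.5 | 22% | 9% | 41% | 44% | 44% | 56% |
| 0.7 | 27% | 3% | 35% | 68% | 44% | 73% |
| 0.8 | 29% | 1% | 32% | 86% | 44% | 86% |
| 0.9 | 31% | <0.1% | 30% | 99% | 44% | 99% |

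**Check by simulation** (3,000 null and 2,000 alternative runs per rho, 0.5 to 0.95; effect sized so that ANCOVA has 90% power).

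- Ordinary ANOVA, group effect: type I error 21 to 32%. Kruskal-Wallis on all scores pooled: 21 to 31%.
- Ordinary group-by-time test: power 39% at rho 0.5, 2% at 0.8 and 0% at 0.9.
- Mixed ANOVA, group-by-time: type I error 4.3 to 5.5%, power 83 to 92%.
- Mixed ANOVA, group main effect: type I error about 5%, but power from 74% at rho 0.5 down to 12% at 0.95.
- Kruskal-Wallis on one post-treatment score: type I error about 5%; power 77%, 61%, 49% and 28% at rho 0.5, 0.7, 0.8 and 0.9.
- Kruskal-Wallis on change from baseline: power 77 to 87%.

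**Normality check.** A two-stage rule (corrected Kolmogorov-Smirnov test, then t test or Kruskal-Wallis on one score; 2,000 runs) gave type I error of 4.5 to 6.2% over a normal, a skewed and a bimodal distribution, with simulation error of about 0.5 points. That is no material inflation. For a mildly skewed bounded score, beta(2, 1.2), the check rejected in 35% of samples of 75 and 70% of samples of 150, so which branch is taken can be a matter of chance.

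**The case against.** The strongest reply is that 2-way ANOVA is shorthand. With two arms and four evaluations, the evident factors are group and time, and the hypothesis is a group-by-time question. Under that reading the test holds 5%, uses the pre-treatment score, and is close to ANCOVA in power at correlation 0.7 and above. This stands. A reader might infer that the planned test must have a wrong error rate or must lose most of its power, and the protocol does not support that. It does not, however, state this model or this contrast, and the same model also yields the much weaker group main effect.

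A reader might also infer that baseline is ignored. That is too strong: section 2.8 has a pre-to-post effect size, and either test could be run on change, where the rank version keeps 77 to 87% power in the simulation. What holds is that no stated test adjusts for baseline.

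The power loss of a post-only rank test depends on a correlation that the protocol does not give. In the simulation it is 13 to 30 points below 90% at correlation 0.5 to 0.7, and most of the power goes only at about 0.9 or more.

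A reader might further infer that the Kolmogorov-Smirnov step inflates the error rate, or that the baseline significance tests are themselves an error. The first is not borne out by the simulation, and no error is shown for the second.

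Finally, model detail may sit in an analysis plan that is not shown. Covariance structure and similar detail can be left there. But the protocol does name its tests and the rule for choosing between them, and these do not fit the design as named.

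**Conclusion.** The point holds as a badly fixed analysis, not as proof that the trial's test is invalid. The wording admits analyses with a type I error from 5% to about 32%. For an assumed 0.3 SD effect at an assumed correlation of 0.8, the power of those analyses runs from about 1% (ordinary group-by-time) through 32% (mixed-model group main effect) and 44% (post-only rank test) to 86% (mixed-model group-by-time). Nothing in section 2.8 selects among them.

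The nonparametric branch has no form that tests group-by-time, so the normality check settles the hypothesis as well as the method. The figures rest on normal data, equal correlation, complete follow-up and a constant effect after treatment. The direction of the ordinary-ANOVA errors needs only positive correlation within a child; their size depends on its value.

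**What to change.** In section 2.8, replace the sentence that names the two tests with wording such as: *GMFM-88 and PBS will each be analysed with a mixed model for repeated measures on the post-intervention scores, with group, visit, group-by-visit and baseline score as fixed effects and correlation within child allowed for. The treatment effect is the between-arm difference, with its 95% CI, at the primary visit.* ANCOVA on the score at that visit, with baseline as covariate, is an acceptable simpler form.

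Three consequential changes follow:

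- The sponsor names the primary visit before analysis, in section 2.6 as well as 2.8, since none is named now.
- The Kolmogorov-Smirnov test is removed as the rule for choosing the primary test. Rank-based analysis, preferably on change from baseline, stays as a sensitivity analysis.
- The effect size is redefined as the between-arm difference from the same model.

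The cost is wording and one decision on the visit. No extra measurement or child is needed. The rule of repeating the previous evaluation for missing scores must also be reconciled with the mixed model, which uses the observed scores as they are.
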